Therefore, the present multicenter randomized controlled trial (RCT) aims to implement and evaluate a personalized CA-CRT program for individuals with AN as an adjunct to standard nutritional rehabilitation (treatment as usual, TAU). The study will test the feasibility and efficacy of CA-CRT in enhancing selected neuropsychological outcomes (cognitive flexibility and central coherence) and psychological measures (eating disorder symptomatology, health-related quality of life, and motivation to change) among inpatients with AN. The feasibility of the study will be evaluated through indices such as the recruitment and retention rates and the patient outcomes. These metrics will help determine not only whether the intervention is acceptable but also whether it can be implemented in routine clinical settings. By delivering a structured, scalable, and individually tailored intervention, the trial seeks to promote more effective, patient-centered care approaches. It is hypothesized that participants allocated to the experimental group will demonstrate greater improvements in the targeted outcomes compared to those receiving standard care alone over the 5-week intervention period. Specifically, the primary hypothesis is that participants in the CA-CRT group will show significantly greater improvement from baseline to post-treatment than those in the TAU group in relation to cognitive flexibility, as measured by the Wisconsin Card Sorting Test (WCST), the Phonemic/Semantic Alternate Fluency Test, the Trail Making Test (TMT), the Test of Attentional Performance (TAP), the Detail and Flexibility Questionnaire (DFlex), and the Cognitive Flexibility Inventory (CFI). Improvements are also expected in the Central Coherence Index (CCI) of the Rey–Osterrieth Complex Figure (ROCF-C).

The secondary hypothesis is that the CA-CRT group will show greater reductions in their eating disorder symptoms (EDE-Q), as well as greater improvements in their quality of life (WHOQOL-BREF) and readiness to change (URICA), compared to those receiving TAU.

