## 2. Materials and Methods

The study will be conducted as a multicenter randomized controlled trial across three specialized Italian facilities dedicated to the nutritional rehabilitation and treatment of those with eating and weight disorders: IRCCS Istituto Auxologico Italiano in Piancavallo Oggebbio (VB), Beato Palazzolo Hospital in Bergamo, and the Mariconda Regional Eating Disorders Unit in Salerno.

Participants who meet the inclusion criteria will be enrolled on a rolling basis and randomized in a 1:1 ratio into two groups using a secure, computerized, web-based system. The experimental group will receive the CA-CRT intervention in addition to the standard rehabilitation program (treatment as usual, TAU), while the control group will follow TAU alone.

In line with national guidelines, the standard TAU protocol will be applied consistently across all the participating sites [45].

The study was registered on ClinicalTrials.gov NCT05912036 (https://clinicaltrials.gov/study/NCT05912036) on 20 June 2023 and follows the SPIRIT Statement for reporting a randomized trial protocol. The corresponding SPIRIT checklist is included as a supplementary document (see Supplementary Table S1).

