### 2.4. Randomization and Blinding

Randomization will be stratified by center and performed using the permuted block technique within each site by a researcher independent of the study. Due to the nature of the intervention, the group allocation cannot be concealed from the participants or the provider of the intervention. Participants will be assigned to one of two conditions within the first week from the baseline assessment (Figure 1).

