Moreover, the Standard Progressive Matrices (SPM) [54,55] will be administered. It consists of 60 items measuring nonverbal intelligence divided into 5 sheets (12 items each). Each item requires completion of a series of figures with a missing part that is presented among distractors, according to an increasing difficulty criterion.

Then, the Italian versions of the following neuropsychological tests will be collected pre- and post-treatment and used as the primary outcomes.

The Wisconsin Card Sorting Test (WCST) [56,57] will be used to assess abstract reasoning, mental flexibility, and problem-solving. The examinee has to match stimulus cards to one of four category cards. Cards can be matched by shape (cross, circle, triangle, star), color (red, blue, yellow, green), and number (one, two, three, four). The rule must be worked out by the feedback provided by the examiner (“right” or “wrong” response). When a rule is identified (i.e., 10 consecutive correct matches), the examiner changes the criterion without saying anything, and the examinee has to identify the new rule. Scoring provides the following indices: total mistakes, total correct responses, completed categories, perseverative mistakes, non-perseverative mistakes, percentages of perseverative mistakes, attempts to complete the first category, inability to retain the criterion, and task learning.

The Phonemic/Semantic Alternate Fluency Test [58] will be used to assess the verbal set-shifting ability. The examinee has to produce word pairs unusually, starting from a phonemic cue (letter A, F, S) and a semantic cue (color, animal, fruit), in 60 s. The raw score (number of word pairs obtained for each association (A–color; F–animal; S–fruit)) is adjusted for age, education, and gender; thus, it is converted into an equivalent score. Moreover, a composite shift index evaluating working memory is determined as follows: Total Alternate Fluencies/(Total Phonemic Fluencies + Total Semantic Fluencies/2).

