Each subtest is preceded by a run-in, and the difficulty level of the task may change, according to the examiner’s guide. The TAP subtests are measured by the reaction times and accuracy determined as correct responses, false responses, omissions, and anticipations (i.e., responses within 100 ms).

The Detail and Flexibility Questionnaire (DFlex) [64,65]: A self-report questionnaire consisting of 24 items on a 6-point Likert scale (from 1 = strongly disagree to 6 = strongly agree) and assessing cognitive rigidity (RC, 12 items) and attention to detail (AD, 12 items). The subscale scores range from 12 to 72 and are calculated by summing the RC items and the AD items.

The Cognitive Flexibility Inventory (CFI) [66,67]: A self-report questionnaire consisting of 20 items used to assess two different subscales: the Alternative subscale, which evaluates the ability to perceive multiple alternative explanations for life events and human behavior, and the ability to generate multiple alternative solutions to difficult situations; and the Control subscale, which assesses the tendency to perceive difficult situations as controllable. Each item is scored on a 7-point Likert scale (from 1 = strongly disagree to 7 = strongly agree). The scoring requires inverse scoring of the selected items. The total score is calculated by the sum of all the items. Higher scores indicate greater cognitive adaptability and flexibility to be used in stressful situations; lower scores indicate greater cognitive rigidity associated with less cognitive flexibility in stressful situations.

The Italian versions of the following psychological measures will be also collected pre/post-treatment and used as secondary outcomes.

The Eating Disorder Examination Questionnaire (EDE-Q) [68,69] is a self-report questionnaire consisting of 33 mixed-type items (yes/no, 7-point Likert scales and visual analog scales) assessing the core symptoms of the eating disorder in the past 28 days. The EDE-Q has four subscales (i.e., Restraint, Eating Concern, Shape Concern, and Weight Concern) and a global score is calculated by the mean of all four subscales. Higher scores indicate an elevated frequency or clinical severity of eating disorder symptoms.

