### 2.6. Procedure

Patients with AN will be invited to take part in the study at admission to the rehabilitation centers, according to the above-mentioned inclusion/exclusion criteria.

Before the randomization, they will be asked to sign the informed consent to participate in the study and to complete the psychodiagnostic (BAI, BDI II, OCI-R) measures.

Randomization will then be stratified by center and performed using the permuted block technique within each site by a researcher independent of the study. Participants will be assigned to one of two conditions: both groups will receive the usual hospital care (TAU), and the experimental group, in addition, will receive the CA-CRT treatment.

Before starting the program, all the participants will undergo neuropsychological testing (primary measures) and complete self-report psychological questionnaires (secondary measures).

The standard nutritional rehabilitation program is set up as a multidisciplinary treatment approach merging group therapies, individual therapies, and dietetic management in line with national guidelines [45]. Dietetic rehabilitation aims to encourage a change in eating habits and includes mealtime supervision, as well as both individual and group counseling provided by dietitians.

Individual sessions last from 30 to 45 min and encompass dietary assessment, evaluation of nutrient intake and adequacy, nutritional and anthropometric status, eating patterns, weight history, and patients’ readiness to change. Group meetings of around 20 people are provided every week and last about one hour. The main topics discussed include biological hunger, satiety, nutrients, weight management, and behavior change strategies for preventing relapse.

The patients’ meal plan is determined by the dietitian to gain half a kilogram (one pound) per week.

Meals last 60 min, followed by a 30 min mandatory resting period, where patients and staff members are together in a dedicated room. There are staff members present at all times during the meal and resting period.

Psychotherapy is provided once a week by a licensed psychotherapist in an individual setting and lasts about 45 min. Further, 1 h psychoeducational groups led by educationalists, psychologists–psychotherapists, or psychiatrists and focused on the relationship between food and emotions are provided weekly.

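### Two self-report questionnaires (DFlex, CFI) are listed among the primary neuropsychological tests of an unblinded trial and share one MANCOVA with the performance tests, so self-ratings could drive a positive primary result

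*Protocol article*

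**What the plan says.** In the protocol article, section 2.5 opens the primary list with "the following neuropsychological tests will be collected pre- and post-treatment and used as the primary outcomes". The list covers WCST, alternate fluency, TMT, ROCF-C and TAP, then runs on to "The Detail and Flexibility Questionnaire (DFlex) [64,65]: A self-report questionnaire consisting of 24 items on a 6-point Likert scale" and "The Cognitive Flexibility Inventory (CFI) [66,67]: A self-report questionnaire consisting of 20 items". Only after these two does the text turn to the secondary outcomes: "The Italian versions of the following psychological measures will be also collected pre/post-treatment and used as secondary outcomes". Those are EDE-Q, WHOQOL-BREF and URICA.

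The Introduction agrees with that order. Its primary hypothesis on cognitive flexibility ends its list of measures with "the Detail and Flexibility Questionnaire (DFlex), and the Cognitive Flexibility Inventory (CFI".

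Section 2.6 draws the line by type of instrument. Before the program starts, "all the participants will undergo neuropsychological testing (primary measures) and complete self-report psychological questionnaires (secondary measures").

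On blinding, section 2.4 says that "the group allocation cannot be concealed from the participants or the provider of the intervention". On the comparator, section 2 says that "the control group will follow TAU alone". Section 2.7 enters neuropsychological and psychological scores together as dependent variables in a MANCOVA. Its reason for a joint model names only WCST, alternate fluency, TMT and ROCF-C.

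**The concern.** DFlex and CFI are primary by the list in section 2.5 and secondary by the type named in section 2.6. The label also affects conduct: section 2.5 has psychological measures completed in groups and neuropsychological tests given individually, so it decides which session holds these two forms.

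The larger issue is what a positive result would mean. Independent assessors and a blinded statistician, both planned, do not protect a form that an unblinded patient fills in about herself. Only the experimental arm receives the 10 + 15 = 25 additional individual sessions, which encourage patients to reflect on how they process information. A group difference on self-rated flexibility could come from knowing the allocation, without any change in set-shifting. With the self-ratings in the same multivariate test as the performance tests, and no stated rule on which measures must improve, that difference alone could make the primary test significant.

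**Working it through.** **Inputs from the article.** Two-sided alpha 0.05, power 0.95, Pillai V = 0.2, effect size 0.5 and 54 patients per center (27 per group) are from section 2.3. Three centers and 1:1 allocation are from section 2. The total over the centers is 3 × 54 = 162.

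**The plan's own figure.** For a group-by-time interaction with two groups and two times, f² = V/(1 − V) = 0.2/0.8 = 0.25, so f = 0.5. With λ = f²N and F on 1 and N − 2 degrees of freedom, N = 54 gives λ = 13.5 and power 0.9501, while N = 53 gives 0.946. The stated 54 reproduces. It models one response at two times, so it does not change when DFlex and CFI change role.

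**Assumptions for the illustration.** The article gives no bias size. Assume no true effect on any measure. Assume that the DFlex and CFI change scores, oriented so that improvement is positive, shift by d = 0.2 SD in favor of the experimental arm, that nothing else shifts, and that all pairs of variables have the same correlation ρ.

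**One score alone** (not the planned test, shown for scale). The noncentrality of a two-sided z-test is d√(N/4).
- N = 162: 0.2 × √40.5 = 1.27, so 24.7% significant. With d = 0.1 and 0.3 the rates are 9.8% and 48.0%.
- N = 54: 0.2 × √13.5 = 0.73, so 11.4%. With d = 0.1 and 0.3 the rates are 6.6% and 19.7%.

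**Omnibus test, closer to section 2.7.** With p dependent variables, two of them shifted, the squared multivariate distance is

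D² = [2d²/(1 − ρ)] × [1 − 2ρ/(1 + (p − 1)ρ)],

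with λ = D²N/4 and F on p and N − p − 1 degrees of freedom. Covariates are ignored.

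Example: p = 7, ρ = 0.5, d = 0.2. D² = (0.08/0.5) × (1 − 1/4) = 0.12. At N = 162, λ = 0.12 × 40.5 = 4.86 on 7 and 154 degrees of freedom, and the rejection rate is 29%.

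The value of p is not fixed by the article. One score for each of the seven measures listed as primary gives 7. Section 2.5 lists nine WCST indices and several TAP scores, and section 2.7 adds the psychological measures, so 20 and 30 are also shown. Each range runs over ρ = 0 to 0.5.

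| Variables p | N = 162 | N = 54 |
|---|---|---|
| 7 | 20–29% | 9–11% |
| 20 | 12–20% | 7–8% |
| 30 | 10–17% | 6–7% |

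The nominal rate is 5%. Under the same assumptions, a test of the performance measures alone stays at 5%, because none of them is shifted.

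**The case against.** **The contradiction.** A reader might infer that the article flatly contradicts itself. It does not go that far. The article mostly sorts outcomes by construct: the Introduction sets cognitive flexibility and central coherence against eating disorder symptoms, quality of life and motivation. The sentence in section 2.6 is a one-line summary that names no instrument and can be read as meaning EDE-Q, WHOQOL-BREF and URICA, while two other places name DFlex and CFI as primary. This stands. What remains is inconsistent wording that needs reconciling.

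**Expectancy alone confirming the hypothesis.** A reader might also infer that expectancy by itself would confirm the primary hypothesis. The documents do not support that. The plan is a MANCOVA, not a separate test of each score, and nothing says that one significant questionnaire suffices. Neither size nor direction of bias is given: the Introduction says that CRT raises awareness of cognitive style, which could also raise self-rated rigidity. The match between session content and items is not shown either. The CFI is described as covering alternative explanations and perceived control. The inflation falls as more variables enter the model, and at N = 54 it is slight.

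**Relabelling is not enough.** While section 2.7 keeps every score in one model, a change of label alone leaves the test as it was. This stands, and the fix therefore reaches the analysis.

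**Performance tests are not a clean refuge.** Table 1 includes sorting cards by color, shape or number, and switching between categories along the alphabet. These resemble WCST and alternate fluency, and only the experimental arm practices them. This stands as a limitation. It does not make unblinded self-ratings a better primary measure.

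**Defensible choice.** Self-rated flexibility is worth measuring where blinding is impossible. It can be kept without serving as primary evidence.

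**Conclusion.** The concern holds in a limited form. DFlex and CFI are unblinded self-ratings placed among the primary neuropsychological tests, section 2.6 leaves their role unclear, and the joint MANCOVA lets them contribute to a positive primary result. Under the assumed 0.2 SD shift on these two measures, with no true effect, the false-positive rate is about 10% to 29% with 162 patients and 6% to 11% with 54, against 5%. These rates rest on the assumed size and direction of the shift, on 7 to 30 variables and on a common correlation of 0 to 0.5. They show what could happen and do not predict it. A decision rule may stand in a fuller document that is not shown. The point rests on the labels and the single model that the article does state, and the correction is cheap enough to be worth making.

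**What to change.** 1. Reconcile the Introduction and sections 2.5 and 2.6: make DFlex and CFI secondary, described as patient-perceived flexibility and attention to detail.
2. Amend section 2.7 so that the primary MANCOVA contains only the performance tests (WCST, alternate fluency, TMT, TAP, ROCF-C). Analyse DFlex, CFI, EDE-Q, WHOQOL-BREF and URICA separately.
3. State that self-ratings alone cannot support the primary claim.
4. Add two limitations to section 3: self-ratings are made with allocation known, and some training exercises resemble WCST and alternate fluency, so the performance tests are not free of practice effects.

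Settle this before outcome data are seen. The cost is a text amendment, with the registry entry updated if it carries the same list. There are no extra data or visits, and the stated 54 per center is unaffected. The downside is that a gain on DFlex or CFI no longer counts as primary evidence.

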### 2.6. Procedure

Patients with AN will be invited to take part in the study at admission to the rehabilitation centers, according to the above-mentioned inclusion/exclusion criteria.

Before the randomization, they will be asked to sign the informed consent to participate in the study and to complete the psychodiagnostic (BAI, BDI II, OCI-R) measures.

Randomization will then be stratified by center and performed using the permuted block technique within each site by a researcher independent of the study. Participants will be assigned to one of two conditions: both groups will receive the usual hospital care (TAU), and the experimental group, in addition, will receive the CA-CRT treatment.

Before starting the program, all the participants will undergo neuropsychological testing (primary measures) and complete self-report psychological questionnaires (secondary measures).

The standard nutritional rehabilitation program is set up as a multidisciplinary treatment approach merging group therapies, individual therapies, and dietetic management in line with national guidelines [45]. Dietetic rehabilitation aims to encourage a change in eating habits and includes mealtime supervision, as well as both individual and group counseling provided by dietitians.

Individual sessions last from 30 to 45 min and encompass dietary assessment, evaluation of nutrient intake and adequacy, nutritional and anthropometric status, eating patterns, weight history, and patients’ readiness to change. Group meetings of around 20 people are provided every week and last about one hour. The main topics discussed include biological hunger, satiety, nutrients, weight management, and behavior change strategies for preventing relapse.

The patients’ meal plan is determined by the dietitian to gain half a kilogram (one pound) per week.

Meals last 60 min, followed by a 30 min mandatory resting period, where patients and staff members are together in a dedicated room. There are staff members present at all times during the meal and resting period.

Psychotherapy is provided once a week by a licensed psychotherapist in an individual setting and lasts about 45 min. Further, 1 h psychoeducational groups led by educationalists, psychologists–psychotherapists, or psychiatrists and focused on the relationship between food and emotions are provided weekly.

Bodily experience is also specifically targeted through body image therapy (provided twice a week for 30 min by physiotherapists) and group dance therapy (provided once weekly by a psychologist and lasting 1 h) to help patients cope with a distorted body image.

Lastly, low-intensity physical activity based on gentle gymnastic sessions (3 times per week, 30 min per session) is provided to treat and normalize patients’ views and attitudes toward physical activity. Tailored activities in both individual and group settings are planned upon physical and functional assessment by professional physiotherapists.

The CA-CRT treatment will entail cognitive exercises aimed at improving more adaptive thinking styles, encouraging patients’ reflection on their way of elaborating information, and exploring the possibility of implementing new schemas in everyday life. The CA-CRT program will employ a wide range of cognitive tasks to address cognitive inflexibility and weak central coherence using the Italian translation of the CRT original manual [72]. The combined treatment will consist of 10 individual 40 min CA-CRT sessions, 2 times a week for 5 weeks, plus 15 individual CA-CRT 30 min sessions, 3 times a week for 5 weeks.

The description of the CA-CRT exercises for each session is reported in Table 1. The CA-CRT will consist of executive functions tasks, i.e., “sequence of symbols” and “answers by category”, as well as visual–perceptual processing, i.e., “figure memory”, and “geometric figure grids” retrieved from the Erica^®^ software (Giunti O.S., Florence, Italy). 

The total duration of the research will be 6 months, considering a discontinuous enrollment related to the patients’ admission to the clinics.

At the end of the treatment (after 5 weeks), recruited participants in both conditions will be administered the neuropsychological tests and the psychological questionnaires again.

Adherence will be supported through participant education and monitored via scheduled assessments and treatment logs.

As the study will be conducted in an inpatient unit with close clinical supervision, a formal monitoring plan is not required.

The experiential treatment can be discontinued in response to adverse events, participant request, or clinical changes. Participants will receive appropriate medical care for any trial-related harm.

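### Section 2.6 lists the pre-treatment measurement of every outcome after open-label randomization, and sections 2.4 and 2.5 can be read otherwise; the outcome baseline should be placed explicitly before allocation

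*Protocol article*

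**What the plan says.** Section 2.6 of the protocol article is the only step-by-step account of the sequence.

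- **Before randomization.** "Before the randomization, they will be asked to sign the informed consent to participate in the study". At this same step, patients are also asked "to complete the psychodiagnostic (BAI, BDI II, OCI-R) measures". None of these three scales is an outcome.
- **Randomization and assignment.** "Randomization will then be stratified by center and performed using the permuted block technique within each site". The two conditions are then described.
- **Outcome baseline.** "Before starting the program, all the participants will undergo neuropsychological testing (primary measures) and complete self-report psychological questionnaires (secondary measures".

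Three other sections bear on this.

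- **Section 2.4** says that "the group allocation cannot be concealed from the participants or the provider of the intervention". It also says: "Participants will be assigned to one of two conditions within the first week from the baseline assessment", with a reference to the flowchart, which is not available in the text reviewed.
- **Section 2.5** uses the word baseline for the psychodiagnostic scales and calls the outcomes pre- and post-treatment measures. It places the psychodiagnostic and psychological questionnaires together in group sessions and neuropsychological testing in individual sessions. The whole assessment is two sessions on consecutive days.
- **The Introduction and section 2.7** define the effect as a between-group difference in improvement from baseline to post-treatment. It is tested in a MANCOVA with group and time as factors and the outcome scores as dependent variables. The covariates are the psychodiagnostic scores, not the outcomes' own baselines.

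**The concern.** A baseline protects a randomized comparison because allocation cannot have influenced it. If section 2.6 is followed as written, that protection is not assured for any primary or secondary outcome: a participant may already have been told the arm when tested. Several of these measures are self-reports (DFlex, CFI, EDE-Q, WHOQOL-BREF, URICA), and the performance tests depend on effort.

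In a group-by-time analysis the pre-treatment score is half of the contrast. A difference between arms created at baseline by knowledge of allocation is then counted as a difference in change. The blinded statistician in section 2.7 gives no protection, because the distortion would already be in the data. No later analysis can recreate a baseline taken before allocation.

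**Working it through.** **1. Order of events.** Section 2.6 ties the psychodiagnostic scales to the time before randomization and the outcome measures to the time before the program starts, with randomization described in between. Nowhere does the article expressly place an outcome measure before allocation. Two statements must be set against this:

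- *Section 2.4* puts assignment after a baseline assessment. If that means the psychodiagnostic scales, which is how section 2.5 uses the word, it agrees with section 2.6 and the outcomes are still measured after allocation. If it means the outcome battery, it contradicts section 2.6.
- *Section 2.5* groups the psychodiagnostic and psychological questionnaires together. If they share one session, EDE-Q, WHOQOL-BREF and URICA would be completed before randomization along with BAI, BDI-II and OCI-R. Section 2.6 splits them around randomization.

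**2. The plan's own sample size.** With Pillai V = 0.2, f² = 0.2/(1 − 0.2) = 0.25, so f = 0.5, as section 2.3 states. For two groups and two times, df = 1 and 52 and λ = 0.25 × 54 = 13.5. Power is 0.9501, so 54 per center is reproduced. Three centers give 3 × 54 = 162. The order of measurement does not affect this figure.

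**3. How a shift enters the effect.** Score each outcome so that higher is better. Let s_pre and s_post be the allocation-driven differences (CA-CRT minus TAU) at the two times. The bias in the group-by-time effect is s_post − s_pre. It equals the full baseline shift in size only if s_post = 0, and it is zero if the shift persists unchanged.

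**4. Illustration for one outcome.** Assumptions, none of them from the document: no true effect, baseline-only shift d in SD units, pre-post correlation ρ, equal variances, no covariates. SD of change = √(2(1 − ρ)), which is 1.000 at ρ = 0.5 and 0.775 at ρ = 0.7. Noncentrality = d / (SD of change × √(2/n)), with n per arm, in a two-sided 5% t test.

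For d = 0.2, n = 27 and ρ = 0.5: 0.2/(1.000 × 0.272) = 0.73. For n = 81: 0.2/(1.000 × 0.157) = 1.27.

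| Shift d | ρ | Type I error, 27 per arm | Type I error, 81 per arm |
|---|---|---|---|
| 0.1 | 0.5 | 6.5% | 9.7% |
| 0.1 | 0.7 | 7.5% | 12.9% |
| 0.2 | 0.5 | 11.1% | 24.4% |
| 0.2 | 0.7 | 15.4% | 37.2% |

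A normal approximation gives 24.7% and 37.6% for the last two entries in the right-hand column.

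**5. Direction.** If knowledge of allocation lowers TAU baselines through disappointment and raises CA-CRT baselines through expectation, then s_pre > 0. With s_post = 0 the bias is negative, against CA-CRT. At noncentrality 1.27, the chance of falsely declaring CA-CRT superior is about P(Z > 1.96 + 1.27) = 0.06%, against a nominal 2.5%. Almost all the false rejections would favor TAU. Other mechanisms could reverse the sign.

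**6. Would adjustment repair it?** Adjusting for the outcome's own baseline reduces the bias to ρ × d. For d = 0.2 this is 0.10 to 0.14 SD, with type I error 7.0-10.9% at 27 per arm and 11.3-23.6% at 81. The bias is smaller but not removed.

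**The case against.** The strongest reply is that section 2.6 is loosely ordered prose, not a schedule. Its sentence on outcome testing is anchored to the start of the program, section 2.4 places a baseline assessment before assignment, and section 2.5 suggests joint questionnaire sessions. The flowchart might settle the matter. This stands as far as it goes: a baseline taken after randomization is what section 2.6 describes, not what the trial is known to do. It does not remove the point, because no section says that outcomes are measured first and the most detailed section lists them last.

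A reader might draw stronger conclusions that the document does not support:

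- *Participants already know their arm at baseline.* Section 2.4 says that allocation cannot be concealed, but no section says when participants are told.
- *Sections 2.4 and 2.6 flatly contradict each other.* They do so only if the baseline assessment in section 2.4 includes the outcome battery.
- *The design will produce false claims of benefit.* The sign is unknown, and the most obvious mechanism works against CA-CRT. Full transfer of the shift also requires that it has disappeared by post-test, whereas knowledge of allocation continues.
- *Participants will be lost between randomization and baseline testing, or assessors are unblinded.* Both go beyond the text. Participants are inpatients recruited in their first week, and the assessors are described as independent of the study. Assessor blinding is a detail that an article may leave to the full protocol.

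**Conclusion.** The concern holds as a defect in the stated sequence. Followed as written, section 2.6 exposes the baseline of every primary and secondary outcome to possible knowledge of allocation; read together with sections 2.4 and 2.5, the order is at best inconsistent. Bias is possible, not shown, and neither its size nor its direction can be derived from the document. The illustrative error rates for a 0.2 SD shift, 11-15% with 54 participants and 24-37% with 162, rest on an assumed shift confined to baseline, an assumed correlation of 0.5 to 0.7 and no true effect. They show that a modest shift would matter; they do not predict one. The point deserves action because it touches all outcomes, cannot be undone once data are collected and costs very little to prevent.

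**What to change.** Amend section 2.6 so that consent and both baseline sessions, covering the psychodiagnostic, neuropsychological and self-report measures, are complete before the allocation is generated and released. In section 2.4, define the baseline assessment as this full battery. In section 2.5, state which questionnaires are completed in which session, so that all three sections and the flowchart give one order.

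The cost is a short amendment and a delay of about one or two days before allocation is released, since the assessment already takes two consecutive days. The sample size stays at 54 per center, and no measure or staff is added. With the baseline taken first, the shift due to knowledge of allocation is zero by design, and this source of type I error inflation is removed.
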